#### **7.1.1. Prior medications related to COVID-19**

The total number of prior medications related to COVID-19 and the number and percentages of patients with at least one prior medication related to COVID-19 will be summarized by treatment group and overall. The number and percentages of prior medications related to COVID-19 will be summarized by anatomical therapeutic chemical (ATC) classification category (level 4), preferred term, treatment group and overall for the Safety Set.

#### **7.1.2. Concomitant medications related to COVID-19**

The total number of concomitant medications related to COVID-19 and the number and percentages of patients with at least one concomitant medication related to COVID-19 will be summarized by treatment group and overall. The number and percentages of concomitant medications will be summarized by ATC classification category (level 4), preferred term, treatment group and overall for the Safety Set.

### **7.2. Extent of Exposure**

Duration of exposure to study drug will be calculated in hours as:

Date and time of end of study drug infusion – date and time of start of study drug infusion.

Duration of exposure to study drug will be summarized by treatment group for all patients in the Safety Set.

The number and percentage of patients who had infusion interruptions will be summarized along with categorical summary of the number of interruptions for patients in the Safety Set.

All study drug information including reasons for drug interruptions will be listed for patients in the Safety Set.

Extent of Exposure data will be presented as well according to the baseline sTREM-1 level (above or equal to the median vs below).

## 8. Efficacy Analyses

The m-ITT set will be used for all efficacy analyses. Main efficacy analyses may be repeated on the ITT and Per Protocol analysis sets.

### 8.1. Analysis of the Primary Endpoint of Part 2: Clinical Status

The clinical status (7-point ordinal scale) at Day 28 will be compared between treatment group using a CMH stratified by baseline clinical status. At baseline, patients are hospitalized on invasive mechanical ventilation or ECMO (Clinical status = 6) or hospitalized, on non-invasive ventilation or high flow oxygen devices (Clinical status = 5).

Patients with a missing clinical status at Day 28 visit and who died prior to or on Day 28 will be assigned the category of 7 at Day 28. Patients with a missing clinical status at Day 28 visit and without documented death occurring prior to or on Day 28 will be assigned the last available clinical status.

The distribution (counts and percentages) of the 7-point ordinal scale will be displayed by treatment group and baseline level (5 or 6) (i.e., the 2x2x7 contingency table).

The 7-point ordinal scale will be compared between treatment groups using a Cochran-Mantel-Haenszel test stratified by baseline clinical status (5 or 6) using modified ridit scores. The Wald test one-sided p-value for the difference in raw mean scores will be provided.

The same analysis will be conducted in patients with a sTREM-1 above the median value at baseline vs below.

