Due to the exploratory nature of this prematurely stopped trial, an adjusted alpha nominal level is proposed for the test of the primary endpoint to take into account the early stop and control the type 1 error at its usual 1-sided level of 0.025. A **conservative** alpha spending function (i.e. the Lan DeMets O'Brien-Fleming spending function) is proposed blind to control the type I error: the nominal 1-sided alpha level considered is 0.003303, derived from the Lan DeMets O'Brien-Fleming spending function at 220 patients (i.e. ~210 patients incorporating the loss of efficiency due to the randomization imbalance in part 1). The choice of this alpha spending function (i.e. the Lan DeMets O'Brien-Fleming spending function) and therefore of a low alpha nominal level of 0.003303 disfavours the rejection of the null hypothesis and can be considered as reasonably conservative compared to the very stringent and highly conservative nominal alpha level of Haybittle Peto (i.e., 0.0001). There is one primary endpoint clearly defined. No adjustment for multiple endpoints will be performed as other endpoints in this prematurely stopped trial are considered as exploratory.

Other p-values derived on secondary endpoints are considered as exploratory only.

Tipping point analyses and multiple imputation approaches may be used as post-hoc analyses if relevant.

Subgroups analyses based on patients baseline sTREM-1 level (above or equal to the median vs below) described in this SAP will be based on calculation performed on the Safety Set.

All analyses will be conducted using SAS Version 9.4 or higher.

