### **4.3. Randomization, Stratification, and Blinding**

#### **4.3.1. Randomization**

The randomization scheme will be generated by an independent statistician who is not part of the study team. A randomization number will be assigned to each patient. The randomization scheme will be generated by a block randomization scheme.

In stage one part 1 of the study, eligible patients were randomized in a 1:1 ratio into 1 of the 2 treatment arms (20 first patients). In stage 2 part 1 of the study, patients were allocated to nangibotide treatment or placebo in a 3:1 ratio resulting in 20 subjects to be randomized on Placebo and 40 subjects randomized on nangibotide at the end of part 1. In part 2 eligible patients will be randomized in a 1:1 ratio into 1 of the 2 treatment arms.

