#### **Sensitivity analyses:**

Primary sensitivity analysis: these will be performed in overall patients and according to the baseline sTREM-1 level (above or equal to the median vs below).

The treatment effect will be estimated in an ordinal logistic regression on the 7-point ordinal scale adjusting for treatment and baseline clinical status assuming odds proportionality. The odds ratio for treatment effect with its 95% confidence interval and p-value will be estimated in this model.

As the odds proportionality may not hold (the p-value of the test for odds proportionality will be provided), the 7-point ordinal scale will be dichotomized in six binary endpoints :  $\leq$  cutoff vs  $>$  cut-off: 1 vs  $>1$ ,  $\leq 2$  vs  $>2$ ,  $\leq 3$  vs  $>3$ ,  $\leq 4$  vs  $>4$ ,  $\leq 5$  vs  $>5$ ,  $\leq 6$  vs  $>6$  (of

note, the last cut-off corresponds to the analysis of mortality at day D28). For each cutoff, treatment groups will be compared by a Cochran-Mantel-Haenszel test stratified by baseline clinical status (5 or 6). Odds ratios (with their 95% confidence intervals and p-values) will also be provided. 2x2x2 contingency tables (counts and percentages) will be provided for each cut-off.

Other sensitivity analyses: these will be performed in overall patients and according to the baseline sTREM-1 level (above or equal to the median vs below) except for analyses stratified by randomization stage.

- 1) The 7-point ordinal scale will be compared between treatment groups using a Cochran-Mantel-Haenszel test stratified by randomization stage (part 1 stage 1, part 1 stage 2 and part 2) and baseline status (5 vs 6). The Wald test p-value for the difference in raw mean scores will be provided.
- 2) The change in the 7-point ordinal scale from baseline to Day 28 will be categorized in two categories: 'improved', 'not improved'.

The distribution (counts and percentages) of the binary scale will be displayed by treatment group and baseline level (5 or 6) (i.e., the 2x2x2 contingency table).

The treatment groups will be compared by a Cochran-Mantel-Haenszel test stratified by baseline clinical status (5 or 6). The odds ratio (with its 95% confidence interval and p-values) will also be provided.

- 3) The change in the 7-point ordinal scale from baseline to Day 28 will be categorized in three categories: 'improved', 'unchanged', 'worsened'.

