## 8.2. Analysis of Mortality at Day 28 (ACM28)

All-Cause Mortality will be assessed using survival status up to study day 31, i.e. any death occurring between the start of study drug infusion and the start of study drug infusion + 30 days.

The number and percentage of patient alive, dead and lost to follow-up at Day 28 will be summarized by treatment group. Any patient with last date known to be alive < Day 28 without death information will be considered lost to follow-up in this summary.

Last known date to be alive will be derived using the following information:

- Death date
- If death date is not documented take the maximum of the following dates:
  - 'Date last known to be alive' documented by the investigator
  - Last patient subject visit date including date of documented follow-up clinical status planned at Day 28 and Day 60
- If derived last known alive date still isn't populated the maximum of the following can be considered:
  - Date of laboratory samples
  - Date of end of organ support
  - Date of end of follow-up, only if reason is completed
  - End date of any adverse events

Inferential analysis will be based on patients which status (alive or dead) is known at Day 28 (i.e. excluding patient lost to follow-up before Day 28). Missing data will not be imputed.

Mortality rate at Day 28 will be compared between treatment group using a CMH adjusted for baseline clinical status (5 vs 6). The common difference in mortality rates between nangibotide and placebo (nangibotide ACM28 rate - placebo ACM28 rate) will be estimated with its 95% confidence interval using the Mantel-Haenszel method. Hence, a negative difference in ACM28 rates favors nangibotide.

This analysis will be done as well according to the baseline sTREM-1 level (above or equal to the median vs below).

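### The primary and Day 28 mortality tests pool stages allocated 1:1, 3:1 and 1:1 without stratifying by stage, so a minor part (up to about 15%) of any outcome drift between stages enters the treatment comparison

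*SAP*

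**What the plan says.** Section 4.3.1 describes three allocation periods. In stage 1 of part 1, "eligible patients were randomized in a 1:1 ratio into 1 of the 2 treatment arms (20 first patients"). Stage 2 of part 1 then ran "in a 3:1 ratio resulting in 20 subjects to be randomized on Placebo and 40 subjects randomized on nangibotide at the end of part 1". Part 2 returned to 1:1. Section 4.2 gives 220 patients at early termination, against 370 planned for the end of part 2.

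The primary test in Section 8.1 pools all of them: "The clinical status (7-point ordinal scale) at Day 28 will be compared between treatment group using a CMH stratified by baseline clinical status", with modified ridit scores. The Day 28 mortality analysis in Section 8.2 has the same structure: "Mortality rate at Day 28 will be compared between treatment group using a CMH adjusted for baseline clinical status (5 vs 6").

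Stage enters in two places only: item 1 of the other sensitivity analyses of clinical status, a CMH "stratified by randomization stage (part 1 stage 1, part 1 stage 2 and part 2) and baseline status (5 vs 6"), and sensitivity analysis 1 of mortality, which is repeated at Day 60. Section 8.1 leaves the stage-stratified analysis out of the sTREM-1 subgroups. The ordinal logistic model adjusts for treatment and baseline status, not for stage.

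Section 4.1 sets the one-sided nominal alpha of 0.003303 at 220 patients, taken as about "210 patients incorporating the loss of efficiency due to the randomization imbalance in part 1".

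**The concern.** When the allocation ratio changes during a trial, randomisation makes the arms comparable within each allocation period, but not across the pooled periods. Here the 3:1 stage is over-represented in the nangibotide arm by design, not by chance. If patients in that stage did better or worse than the others for reasons that baseline status 5/6 does not capture, such as changing standard care or case mix, part of that difference appears as a drug effect.

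This bears on the only test with a controlled error rate, and on the estimated mortality difference. A sensitivity analysis can reveal the problem but cannot restore the error rate of the test judged against 0.003303, and the SAP gives no rule for the case where the two analyses disagree.

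**Working it through.** **Inputs.** From Sections 3.1, 4.2 and 4.3.1: stage 1 has 20 patients (10/10); stage 2 has 40 (30 nangibotide, 10 placebo); part 2 has 220 − 60 = 160 at termination, 70 at the interim look and 310 as planned. Assumption: part 2 splits equally, 80/80 at termination.

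**1. Reproducing the SAP's 210 and 0.003303.** The information of a stage-stratified comparison, in equivalent 1:1 patients, is the sum over stages of 4·n·p·(1−p). Stage 1 gives 20. Stage 2 gives 4 × 40 × 0.75 × 0.25 = 30. Part 2 counts in full.
- Interim: 20 + 30 + 70 = 120
- Termination: 20 + 30 + 160 = 210
- Planned: 20 + 30 + 310 = 360

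Lan-DeMets O'Brien-Fleming spending at one-sided 0.025 is α(t) = 2[1 − Φ(z/√t)], with z the upper 1.25% normal point. It gives α(120/360) = 0.0001035 and α(210/360) = 0.0033389. With the first amount counted as spent at the interim look, the increment is 0.0032354. Solving for the second boundary with correlation √(120/210) gives a nominal level of 0.0033030, which matches the SAP.

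Other bases that were tried do not match:

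| Information basis | Nominal one-sided alpha |
|---|---|
| Stage-stratified, 120/360 then 210/360 | 0.003303 |
| Stage-stratified, single look at 210/360 | 0.003339 |
| Pooled without stage, 126.9/368.9 then 218.2/368.9 | 0.00352 |
| Raw counts, 130/370 then 220/370 | 0.00360 |

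The pooled figures come from 4 × 75 × 55/130 = 126.9, 4 × 120 × 100/220 = 218.2 and 4 × 195 × 175/370 = 368.9.

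**2. Share of a drift that leaks.** This is the difference between arms in stage shares (120 nangibotide, 100 placebo):

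| Stage | Nangibotide | Placebo | Difference |
|---|---|---|---|
| Part 1 stage 1 | 10/120 = 8.3% | 10/100 = 10% | −1.7 points |
| Part 1 stage 2 | 30/120 = 25.0% | 10/100 = 10% | +15.0 points |
| Part 2 | 80/120 = 66.7% | 80/100 = 80% | −13.3 points |

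A 10-point mortality difference confined to stage 2 thus gives 0.15 × 10 = 1.5 points of spurious effect. A 10-point difference between parts 1 and 2 gives 0.133 × 10 = 1.3 points. A stage 1 drift of that size gives about 0.2 points, in the opposite direction.

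**3. Error rate at 0.003303.** The modified-ridit CMH was simulated under no drug effect, with 12,000 trials per scenario. Assumptions: Day 28 category probabilities 0.40, 0.15, 0.05, 0.03, 0.04, 0.08, 0.25 before shifts for baseline status, and 30% of patients at status 6. The table gives the one-sided rejection rate in favour of nangibotide; odds ratios (OR) refer to a worse status.

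| Drift | Planned test | Stage-stratified test |
|---|---|---|
| None | 0.0037 | 0.0031 |
| Stage 2, OR 0.5 | 0.0102 | 0.0038 |
| All of part 1, OR 0.5 | 0.0074 | 0.0034 |
| Stage 2, OR 0.33 | 0.0151 | 0.0028 |
| All of part 1, OR 0.33 | 0.0134 | 0.0031 |
| All of part 1, OR 2 | 0.0007 | 0.0032 |

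The simulation standard error at the nominal level is √(0.003303 × 0.996697/12,000) = 0.0005, so the stage-stratified column is consistent with nominal throughout. Separate simulations with other assumed distributions gave about 0.010 to 0.011 for stage 2 at OR 0.5, and 0.0002 to 0.0010 for stage 2 at OR 2. A milder stage 2 drift, OR 0.67, gave about 0.006.

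**The case against.** The strongest reply is that the SAP anticipated the issue. The stage-stratified CMH is pre-specified for clinical status and for mortality, so a reader of the report would see a discrepancy. The dispute is over which of two planned tests is primary. That is fair, and it makes the fix cheap, but only one test is held to 0.003303, and it is the unprotected one.

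Four stronger readings are tempting and are not supported.
- A reader might infer that all drift between stages is counted as treatment effect. At most about 15% is, almost none if the drift is confined to stage 1, and whatever baseline status 5/6 explains is already removed.
- A reader might infer that the SAP contradicts itself and that its alpha is invalid. Section 4.1 uses the 210 only to set the threshold and never says that the primary test is stratified by stage. Against about 0.00352 for the pooled test, 0.003303 is the stricter level, in keeping with the SAP's stated wish to be conservative.
- A reader might infer that the error exceeds 2.5%. It does so only if the test is run at nominal 2.5% (about 6% to 7% for stage 2 at OR 0.5), which the SAP does not do. At 0.003303 the largest simulated value is 1.5%.
- A reader might call the omission of stage in the sTREM-1 subgroups a defect. Each half has about 110 patients spread over six strata, with about 5 stage 2 placebo patients. In simulation about 41% of half-samples had at least one stratum with no two-arm comparison. Leaving stage out there is defensible.

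The documents also give no evidence that a drift occurred, and mortality is exploratory with no alpha attached.

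**Conclusion.** The point holds as a conditional bias of limited size. The primary CMH and the Day 28 mortality CMH are exposed to roughly 13% to 15% of a drift that involves stage 2 or separates part 1 from part 2. If outcomes in the 3:1 stage were better, the one-sided error at 0.003303 rises to about 1.0% at OR 0.5, some three times nominal. If they were worse, the test is biased against nangibotide. The stage-stratified test avoids both.

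Of the information bases tried, only the stage-stratified one with two looks reproduces 0.003303. The threshold therefore appears to have been set for a stage-stratified test: the SAP accepts the efficiency loss of such a test without gaining its protection. The match also requires counting alpha as spent at the 130-patient look, which Section 3.1 describes as a futility assessment.

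The size, direction and existence of drift, the Day 28 distribution, the share at baseline status 6 and the 80/80 split are assumptions. The allocation ratios, the strata of the two tests and the stated alpha come from the SAP.

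**What to change.** - In Section 8.1, make the CMH stratified by randomisation stage and baseline status (existing item 1 of the other sensitivity analyses) the primary analysis, with modified ridit scores. Keep the version without stage as a sensitivity analysis.
- In Section 8.2, make the corresponding stage-stratified CMH the main analysis of Day 28 mortality.
- Add stage as a covariate in the ordinal logistic model for the overall population.
- Leave alpha at 0.003303, which already corresponds to this test. Full stage strata need not be imposed in the sTREM-1 halves.

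The cost is about 3 points of power: roughly 50% against 53% at 0.003303 for a treatment odds ratio of 0.5 with no stage effect, under the assumed distribution.

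Timing matters. The Addendum's Introduction says that the main SAP was approved before unblinding and that the Addendum was written after unblinding and database lock. Exchanging the primary test after unblinding would be a data-aware change. If the main SAP can no longer be amended, report the pre-specified stage-stratified result beside the primary one with equal prominence, and state that the alpha corresponds to the stage-stratified test.

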#### **Sensitivity analyses:**

Primary sensitivity analysis: these will be performed in overall patients and according to the baseline sTREM-1 level (above or equal to the median vs below).

The treatment effect will be estimated in an ordinal logistic regression on the 7-point ordinal scale adjusting for treatment and baseline clinical status assuming odds proportionality. The odds ratio for treatment effect with its 95% confidence interval and p-value will be estimated in this model.

As the odds proportionality may not hold (the p-value of the test for odds proportionality will be provided), the 7-point ordinal scale will be dichotomized in six binary endpoints :  $\leq$  cutoff vs  $>$  cut-off: 1 vs  $>1$ ,  $\leq 2$  vs  $>2$ ,  $\leq 3$  vs  $>3$ ,  $\leq 4$  vs  $>4$ ,  $\leq 5$  vs  $>5$ ,  $\leq 6$  vs  $>6$  (of

note, the last cut-off corresponds to the analysis of mortality at day D28). For each cutoff, treatment groups will be compared by a Cochran-Mantel-Haenszel test stratified by baseline clinical status (5 or 6). Odds ratios (with their 95% confidence intervals and p-values) will also be provided. 2x2x2 contingency tables (counts and percentages) will be provided for each cut-off.

Other sensitivity analyses: these will be performed in overall patients and according to the baseline sTREM-1 level (above or equal to the median vs below) except for analyses stratified by randomization stage.

- 1) The 7-point ordinal scale will be compared between treatment groups using a Cochran-Mantel-Haenszel test stratified by randomization stage (part 1 stage 1, part 1 stage 2 and part 2) and baseline status (5 vs 6). The Wald test p-value for the difference in raw mean scores will be provided.
- 2) The change in the 7-point ordinal scale from baseline to Day 28 will be categorized in two categories: 'improved', 'not improved'.

The distribution (counts and percentages) of the binary scale will be displayed by treatment group and baseline level (5 or 6) (i.e., the 2x2x2 contingency table).

The treatment groups will be compared by a Cochran-Mantel-Haenszel test stratified by baseline clinical status (5 or 6). The odds ratio (with its 95% confidence interval and p-values) will also be provided.

- 3) The change in the 7-point ordinal scale from baseline to Day 28 will be categorized in three categories: 'improved', 'unchanged', 'worsened'.

The distribution (counts and percentages) of the 3-point ordinal scale will be displayed by treatment group and baseline level (5 or 6) (i.e., the 2x2x3 contingency table).

The 3-point ordinal scale will be compared between treatment groups using a Cochran-Mantel-Haenszel test stratified by baseline clinical status (5 or 6) using modified ridit scores. The Wald test p-value for the difference in raw mean scores will be provided. The treatment effect will be estimated in an ordinal logistic regression on the 3-point ordinal scale adjusting for treatment and baseline clinical status assuming odds proportionality. The odds ratio for treatment effect with its 95% confidence interval and p-value will be estimated in this model.

## 8.2. Analysis of Mortality at Day 28 (ACM28)

All-Cause Mortality will be assessed using survival status up to study day 31, i.e. any death occurring between the start of study drug infusion and the start of study drug infusion + 30 days.

The number and percentage of patient alive, dead and lost to follow-up at Day 28 will be summarized by treatment group. Any patient with last date known to be alive < Day 28 without death information will be considered lost to follow-up in this summary.

Last known date to be alive will be derived using the following information:

- Death date
- If death date is not documented take the maximum of the following dates:
  - 'Date last known to be alive' documented by the investigator
  - Last patient subject visit date including date of documented follow-up clinical status planned at Day 28 and Day 60
- If derived last known alive date still isn't populated the maximum of the following can be considered:
  - Date of laboratory samples
  - Date of end of organ support
  - Date of end of follow-up, only if reason is completed
  - End date of any adverse events

Inferential analysis will be based on patients which status (alive or dead) is known at Day 28 (i.e. excluding patient lost to follow-up before Day 28). Missing data will not be imputed.

Mortality rate at Day 28 will be compared between treatment group using a CMH adjusted for baseline clinical status (5 vs 6). The common difference in mortality rates between nangibotide and placebo (nangibotide ACM28 rate - placebo ACM28 rate) will be estimated with its 95% confidence interval using the Mantel-Haenszel method. Hence, a negative difference in ACM28 rates favors nangibotide.

This analysis will be done as well according to the baseline sTREM-1 level (above or equal to the median vs below).

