#### 3.3. Study Endpoints

##### 3.3.1. Primary and Key secondary endpoints

- Primary endpoint of part 2: Clinical status 7-point ordinal scale at Day 28
- Key secondary endpoint of part 2: All-cause mortality at Day 28

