### **Baseline and Study Day**

Unless otherwise specified, baseline (day 1) will be defined as the last non-missing evaluation prior to or on the date that the first dose of treatment is given.

For visits prior to day of first study dose, study day will be calculated as:  
assessment date – first study dose date.

For visits on or after the day of first study dose, the study day will be calculated as:  
assessment date - first study dose date + 1.

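### Mortality at Day 28 (SAP 8.2) counts deaths to study day 31 but requires survivors to be followed only to Day 28

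*SAP*

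**What the plan says.** - **Endpoint.** SAP 3.3.1 lists "Key secondary endpoint of part 2: All-cause mortality at Day 28".
- **Deaths counted.** SAP 8.2, under a Day 28 heading, states "All-Cause Mortality will be assessed using survival status up to study day 31" and explains this as "any death occurring between the start of study drug infusion and the start of study drug infusion + 30 days".
- **Follow-up required of survivors.** The same section states "Any patient with last date known to be alive < Day 28 without death information will be considered lost to follow-up", and then "Inferential analysis will be based on patients which status (alive or dead) is known at Day 28". Patients lost before Day 28 are excluded and nothing is imputed.
- **Primary endpoint.** SAP 8.1 deals with a missing Day 28 status. Patients "who died prior to or on Day 28 will be assigned the category of 7 at Day 28"; all others with a missing status keep their last available one.
- **Stated link between the two.** The sensitivity analyses in 8.1 split the scale at six cut-offs and remark that "the last cut-off corresponds to the analysis of mortality at day D28".
- **Another Day 28 rule.** SAP 8.3.1 sets organ-support-free days to zero for a death on or before Day 28.

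**The concern.** A proportion dead at a fixed time needs one time point for both outcomes. Here a death on study day 29, 30 or 31 is an event, while a patient last seen alive on Day 28 is a full survivor although nothing is known of the next three days. The numerator runs to day 31 and the denominator is fixed at Day 28.

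Two things are at stake. First, the risk difference and its confidence interval would be reported as Day 28 mortality when they are not. Second, the SAP holds more than one rule for who is dead at Day 28, so its tables can disagree. A patient seen alive at a visit on Day 28 who dies on Day 30 has a Day 28 status below 7 and is not set to zero organ-support-free days, yet is dead in ACM28.

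**Working it through.** **1. The SAP's own day count.** For days on or after first dose, study day is "assessment date - first study dose date + 1".
- Start + 30 days: 30 + 1 = study day 31. The SAP's figure is reproduced, so the window is deliberate and not a slip in counting.
- Day 28: 28 − 1 = start + 27 days.
- Excess: 30 − 27 = 3 days (study days 29, 30 and 31).

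**2. The rules side by side.**

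| Rule | Last day that matters |
|---|---|
| ACM28, death counts (8.2) | Day 31 |
| ACM28, survivor must be known alive (8.2) | Day 28 |
| Category 7 when Day 28 status is missing (8.1) | Day 28 |
| Zero organ-support-free days (8.3.1) | Day 28 |
| Kaplan-Meier at Day 28 (8.2) | no separate death window stated |
| Repeat at Day 60 (8.2) | no death window stated |

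**3. Size of the extra window.** The SAP gives no mortality rate, so everything here is assumed except N = 220 (SAP 4.2). Let m be Day 28 mortality and f the hazard on days 29–31 relative to the average over days 1–28.

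Extra = (1 − m) × [1 − (1 − m)^(3f/28)]

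- m = 15%, f = 0.25: 0.37 points, 0.8 deaths in 220.
- m = 25%, f = 0.5: 1.15 points, 2.5 deaths.
- m = 25%, f = 1: 2.28 points, 5.0 deaths.
- m = 40%, f = 1: 3.20 points, 7.0 deaths.

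A second route assumes that mortality rises 5 points over the 32 days from Day 28 to Day 60. The daily hazard is h = −ln[(1 − m60)/(1 − m28)]/32, and the extra is (1 − m28) × [1 − exp(−3hk)]. For 25% to 30%, h = 0.0690/32 = 0.00216. With k = 1 the extra is 0.48 points (1.1 deaths); with k = 2 it is 0.96 points (2.1 deaths). Starting from 20% or 30% gives almost the same.

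Together: about 1 to 7 deaths in 220.

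**4. Effect of the unequal windows.** Take m = 25% and f = 1, so true day-31 mortality is 25 + 2.28 = 27.28%. If a share L of survivors is last seen on days 28–30 and none of their deaths on days 29–31 is captured, the recorded rate is 25 + 2.28 × (1 − L):
- L = 10%: 27.05%.
- L = 50%: 26.14%.

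Both lie between the 28-day and the 31-day figure and equal neither.

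**5. Effect on the treatment comparison.** SAP 4.3.1 gives 40 nangibotide and 20 placebo patients in part 1. If the other 160 split 80/80, the arms are 120 and 100. At 25% mortality the standard error of the difference is √[0.25 × 0.75 × (1/120 + 1/100)] = 5.9 points. Two extra deaths, both on placebo, move the difference by 2/100 = 2.0 points, or 0.34 standard errors.

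**The case against.** The best defence is that the window is explicit, agrees with the study-day formula, applies to both arms alike and was approved before unblinding. SAP 4.1 gives alpha only to the 7-point scale and calls other p-values exploratory. Part 2 patients also have a Day 60 contact that feeds the last-known-alive date, so their status through day 31 will usually be known. All of this stands and limits the weight of the point. It does not remove the mismatch between label, death window and follow-up requirement.

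A reader might infer more than the SAP supports:

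- **That every Day 30 death is alive on the 7-point scale.** The Day 28 death rule in 8.1 covers only a missing status. By-visit data follow the eCRF visit name (4.1), and the Day 28 visit has a +7-day window (11.1), so a form completed late could record category 7 for that death. The +7-day window does not explain day 31 either, since it would reach day 35.
- **That the Kaplan-Meier estimate contradicts ACM28.** Section 8.2 says only that it is read at Day 28, and gives it no separate death rule.
- **That part 1 biases the result.** Note 12 to the schedule in 11.1 limits the Day 60 contact to parts 2 and 3. On the arm sizes assumed above, part 1 makes up 40/120 = 33% of nangibotide and 20/100 = 20% of placebo. Uneven capture of deaths on days 29–31 is therefore possible. Nothing in the SAP sizes it, and a part 1 Day 28 visit may itself fall as late as day 35.
- **That the death window alone makes the tables disagree.** ACM28 excludes patients lost before Day 28, while 8.1 carries the last status forward. The >6 cut-off and ACM28 could differ even with one death window.

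**Conclusion.** The definition in SAP 8.2 is wrong as written for an endpoint called mortality at Day 28: deaths run to day 31 and survivals to Day 28. It also departs from the Day 28 death cut-off in 8.1 (missing status) and 8.3.1, so the claimed correspondence between the >6 cut-off and Day 28 mortality need not hold.

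The size rests wholly on assumption: about 1 to 2 deaths in 220 if mortality rises 5 points between Day 28 and Day 60, and up to about 7 with 40% Day 28 mortality and no fall in hazard. One or two deaths would rarely change a conclusion. With an exploratory endpoint and an effect that is probably small, this is a should-fix and not a threat to the trial's primary test.

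**What to change.** - In 8.2, count as dead only deaths with study day ≤ 28 (start of infusion + 27 days). Count as alive anyone known alive on Day 28 or dying later. Exclude only those whose status at Day 28 is unknown.
- Use that cut-off for ACM28, its denominator, the Kaplan-Meier estimate and the category 7 rule. For category 7, say explicitly how a death after Day 28 recorded on a late Day 28 form is handled.
- For the Day 60 repeat, state death ≤ Day 60.
- Report the pre-specified day-31 window as a sensitivity analysis, labelled day-31 mortality and restricted to patients whose status is known to day 31.
- Reword the note in 8.1: the >6 cut-off and ACM28 also differ in missing-data handling (last status carried forward against lost patients excluded).

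The cost is a few sentences, a date cut-off in the programming and perhaps a handful fewer counted deaths. The main SAP was approved before unblinding and the addendum was written after it, so changing the cut-off now is post hoc. It must be declared so, with both results shown.
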